### Secondary analysis: cribriform cancer detection

We will quantify the concordance of the AI system’s prediction of the presence of cribriform cancer with the reference standards in those internal and external validation cohorts where a reference standard is available (AMU, MUL, SCH, STHLM3, SUH). The tuning set has an insufficient number of cribriform samples for evaluation and will be included in the training. The concordance will be quantified using unweighted Cohen’s kappa. In addition, we will also report AUROC, sensitivity (true positive rate), specificity (true negative rate) and confusion matrices. Slides reported as borderline for cribriform cancer will be considered negative. The analysis will be conducted on slide level. CIs will be computed using the non-parametric bootstrap over cases.

The model will be developed and validated to identify cribriform growth pattern, irrespective of whether it occurs within acinar adenocarcinoma (ie, invasive cribriform) or intraductal carcinoma (IDC) (ie, non-invasive cribriform). The rationale for this is that these entities are often assessed and reported together for further prognostication and treatment planning. This practice is supported by the 2019 ISUP consensus, which recommended incorporating IDC into the Gleason grading when present alongside invasive carcinoma.^46^

### Secondary analysis: PNI detection

We will quantify the concordance of the AI system’s prediction of the presence of PNI with the reference standards in those internal and external validation cohorts where a reference standard is available (MUL, SCH, STHLM3 and SUH). The tuning set has an insufficient number of PNI samples for evaluation and will be included in the training. The concordance will be quantified using unweighted Cohen’s kappa. In addition, we will also report AUROC, sensitivity (true positive rate), specificity (true negative rate) and confusion matrices. Slides reported as borderline for PNI will be considered negative. The analysis will be conducted on slide level. CIs will be computed using the non-parametric bootstrap over cases.

### Subgroup analyses

#### Subgroup analysis A

We will measure the performance of the AI system in terms of the primary and secondary objectives across subgroups of patients divided by age. Analysis will be conducted on the cohorts where age information can be retrieved (online supplemental appendix 2) according to the age groups: <50, 50–59, 60–69 and ≥70.

#### Subgroup analysis B

We will measure the performance of the AI system in terms of the primary and secondary objectives across subgroups of patients divided by biopsy sampling technique (systematic vs targeted vs combined). The analysis will be conducted on the cohorts where biopsy sampling technique information can be retrieved.

#### Subgroup analysis C

We will measure the performance of the AI system in terms of the primary and secondary objectives across subgroups of patients who were treatment-naive or had received treatment for BPH (using, eg, 5-alpha reductase inhibitors) before the biopsy procedure. The analysis will be conducted on the cohorts where treatment information can be retrieved. Some (very few) individuals included in the patient cohorts may also have undergone prior prostate cancer treatment (eg, radiation therapy), but the number of cases is insufficient for a subgroup analysis.

#### Subgroup analysis D

We will measure the performance of the AI system in terms of the primary objective on subgroups of slides representing morphological subtypes of benign and malignant tissue that are usually hard for pathologists to diagnose. We evaluate the performance of the AI system in the STHLM3 morphological subtypes internal validation cohort, the KUH-2 external validation cohort and the AQ external and partly external validation cohorts. See table 4 for the distribution of morphological subtypes reported in each cohort. We will evaluate performance in terms of cancer diagnosis and, additionally, Gleason scoring, where applicable to the subtype.

#### Subgroup analysis E

We will measure the performance of the AI system in terms of the primary objective across subgroups of slides which required IHC staining for confirming the diagnosis and slides which the pathologists could assess without IHC. The analysis will be conducted on the cohorts where information on IHC can be retrieved (see table 5).

#### Subgroup analysis F

We will measure the performance of the AI system in terms of the primary objective in comparison to the state-of-the-art algorithms developed in the PANDA challenge.^17^ The analysis will be conducted on the subgroups of the KUH-1, RUMC and STHLM3 cohorts representing the internal and external validation sets of PANDA. For a fair comparison, we will apply the AI system on the WSIs provided to the challenge participants, which differ in terms of preprocessing and file format from the underlying original WSIs of the KUH-1 and STHLM3 cohorts, which are used in our primary analysis.

We evaluate the performance in the tuning cohort KUH-1 (ie, PANDA European external validation set) and compare the AI system with the PANDA challenge algorithms.We evaluate the performance in the combined PANDA subset of the RUMC and STHLM3 internal validation cohorts (ie, PANDA internal validation set) and compare the AI system with the PANDA challenge algorithms.

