### Study design

The aim of this study is to develop the AI system described above and validate its diagnostic performance on retrospectively collected cohorts. To carry out the study, historical data, including medical records, pathology reports and digitised images, have been collected for cases where both the AI system and human pathologists make diagnostic assessments. The study design involves two independent phases: AI system development and AI system validation as shown in figure 1. The development phase involves an iterative cycle of refining the model design and hyperparameters using predefined development and tuning cohorts for model training and estimation of the effects of design choices on diagnostic performance. Once the overall performance on the development and tuning sets is deemed to have reached a plateau and further changes to the model design no longer yield meaningful improvements, a design freeze will take place and the final AI model will be graduated to the validation phase. This design achieves complete isolation between the model development and the retrospective validation to avoid any information leakage, which could lead to overly optimistic validation results. All model parameters and hyperparameters, including selection of any classifier thresholds, will be set based on the development and tuning cohorts, and no adjustments or tweaking will be conducted on the validation cohorts, which will remain entirely untouched during the development phase. Development data, on the other hand, can be freely accessed without risk of bias at any point, allowing optimisation of the AI model design prior to the validation phase of the study.

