**Figure 1 F1:**
[figure not shown]
Overview of the study design. The study design has two main steps: (top) The development phase involves model design optimisation through an iterative process of experiments. In each experiment, the model is trained and its performance is evaluated on the development set using cross-validation and on a separate tuning set. (bottom) The validation phase is initiated with a design freeze, after which no further changes to the model take place. Validation comprises the assessment on the internal data (ie, collected from the same laboratory and/or using the same scanner as development data) and the external data (ie, collected from other laboratories using other scanners than any of the development data). The colour-coding of the cohort icons represents the shared origin of data used for development and internal validation, and the fully independent nature of the external validation and tuning cohorts. Created in BioRender. [name] (2025) https://BioRender.com/evzu6sn. WSIs, whole slide images.

The development cohorts provide a wide representation of tissue morphologies, scanning devices, laboratories and clinical characteristics of patients, allowing for the training of a robust model. The tuning cohorts enable assessing model generalisation (ie, performance on data from different laboratories and scanners than the development cohorts) on each development iteration, and direct performance comparison with state-of-the-art models evaluated on these same datasets in earlier studies.^15 17^ Sequential experiments will be conducted one modification at a time to evaluate, for example, different preprocessing approaches for extracting image data from the WSI, deep neural network architectures, optimiser hyperparameters, etc (see online supplemental appendix 1). Model performance at each step will be measured using cross-validation on the development cohorts and independent evaluation on the tuning cohorts.

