### Data partitions

#### Requirements for data partition

We established a number of requirements to guide the inclusion, exclusion and partitioning of data into development, tuning and validation sets to account for several sources of potential bias in the training and validation of the model. We followed available guidelines and criteria for balanced and representative data partitions^32 34 39 40^ and arrived at the following set of requirements:

Representative sample selection: Ensure the data are representative of the diversity encountered in clinical practice by including multisite cohorts with variations in scanning equipment (eg, vendors, models, image formats), biopsy preparation (eg, staining, tissue cutting), morphological heterogeneity (eg, different GSs and rare cancer subtypes) and patient demographics.Representative sample size: Include a sufficiently large sample for development and validation to increase the probability of generalisability in the larger population.Mitigate overfitting due to observer bias: Alleviate the possibility of overfitting or ‘over tweaking’ of the model, which may be caused by excessive refinement of the model design aimed at maximising cross-validation performance in development data, since that can jeopardise generalisation outside the development cohorts. The issue can be mitigated by additional (external) tuning data cohorts serving as a less biased performance indicator during model development. It should be further ensured that the tuning cohorts are independent of model training (eg, criteria for early stopping of model training should be assessed only on the development data).Ensure independence of specimens between data partitions: Each data partition (development, tuning, internal or external validation sets) should be independent of the others with no overlap of biopsies or patients.Ensure independence of the sample preparation process between data partitions: Sample external cohorts such that there is no overlap with respect to the clinical laboratories that prepared these cohorts and the development cohorts.Ensure independence of the digitisation process between data partitions: Sample external cohorts such that there is no overlap with respect to the scanning device used for these cohorts and the development cohorts.

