The tuning set was sampled from the following cohorts: Karolinska University Hospital (KUH-1), RUMC and STHLM3. The entire KUH-1 cohort was assigned to tuning and represents a fully external cohort relative to the development set (ie, different patients, laboratory and scanner). This set also corresponds to the European external validation cohort of the PANDA challenge.^17^ The subsets of the RUMC and STHLM3 cohorts assigned to the tuning set represent internal data relative to the development set (ie, different patients but the same laboratories and scanners) and correspond to the PANDA public test sets in Kaggle (ie, the PANDA tuning sets). The tuning sets allow for evaluating the effects of model design changes on data that is independent of the development set, direct comparison with state-of-the-art models from PANDA, and in the case of KUH-1, assessing the generalisation performance of the model prior to design freeze (ie, performance on data coming from different patients, laboratories and scanners compared with the development data) (Requirement 3). A subset of slides belonging to the PANDA Swedish tuning set was allocated to the internal validation set for reasons related to patient stratification and the inclusion of specific subsets of interest in the internal validation (see below).

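### One of the two PANDA comparisons in Subgroup analysis F uses KUH-1, a cohort that helped choose this model's design, so that comparison leans towards the AI system

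*Protocol article*

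**What the plan says.** **Role of KUH-1 in this study.** Under Predefined data partitions: "The entire KUH-1 cohort was assigned to tuning and represents a fully external cohort relative to the development set". The same section identifies it with a PANDA set: "This set also corresponds to the European external validation cohort of the PANDA challenge". Subsets of RUMC and STHLM3 make up the rest of the tuning set.

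**What the tuning set decides.** Study design states: "All model parameters and hyperparameters, including selection of any classifier thresholds, will be set based on the development and tuning cohorts". The freeze follows "Once the overall performance on the development and tuning sets is deemed to have reached a plateau". The text after Figure 1 adds: "Model performance at each step will be measured using cross-validation on the development cohorts and independent evaluation on the tuning cohorts".

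**The limit placed on tuning data.** Requirements for data partition says: "It should be further ensured that the tuning cohorts are independent of model training". Early stopping is given as an example. The same requirement describes tuning cohorts as a less biased indicator, not an unbiased one.

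**The comparison.** Subgroup analysis F plans two comparisons with the challenge algorithms. The first is on KUH-1: "We evaluate the performance in the tuning cohort KUH-1 (ie, PANDA European external validation set) and compare the AI system with the PANDA challenge algorithms". The second is on the combined PANDA subset of the RUMC and STHLM3 internal validation cohorts. Its one stated fairness measure is: "For a fair comparison, we will apply the AI system on the WSIs provided to the challenge participants".

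**The concern.** A head-to-head comparison is even-handed only if the test slides played the same part for both sides. On KUH-1 they did not. The AI system's design was steered partly by its score on these slides, whereas the protocol labels them external validation data for the challenge algorithms. A design retained partly because it scored well on 330 particular slides will, on average, score better on them than on fresh slides of the same kind.

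At stake is how a difference on KUH-1 is read. A lead over the challenge algorithms would mix true performance with selection optimism, and the two cannot be separated afterwards. The label that KUH-1 carries from the challenge makes it easy to read the result as an external one. The protocol's confidence intervals for the grading metrics come from a bootstrap over cases applied to the chosen model. They reflect sampling of slides, not the choice among designs, so they would not show the bias.

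**Working it through.** The protocol gives no sample size, margin or error rate for this comparison, so it has no figure of its own to reproduce. The check is first textual, then an illustration of size.

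**Step 1: the same slides, seen from each side**

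| Question | AI system | Challenge algorithms |
|---|---|---|
| Used to fit weights or for early stopping? | No (Requirements for data partition) | Not described |
| Scored at each design step? | Yes, as part of the tuning set (Study design) | Not described; labelled external validation |
| Part of the basis for thresholds and the freeze? | Yes, with the development cohorts and other tuning subsets (Study design) | Not described; labelled external validation |
| Same image files? | Yes (Subgroup analysis F) | Yes |

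Only the last row is equalised by the plan. That the challenge algorithms were not tuned on KUH-1 is an inference from the label, because their construction is in a source not shown.

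**Step 2: how large could the optimism be?**

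Inputs:
- n = 330 slides (Tables 1 and 2). This is the only input taken from the document.
- K, the number of truly equal candidate designs: assumed 5, 20 or 50. The protocol does not state the number of steps.
- ρ, the correlation between the candidates' KUH-1 scores: assumed 0.8 to 0.9.
- SE of QWK at n = 330: taken as 0.010 to 0.020. A simulation with an assumed ISUP mix (35% benign) and independent slides gave 0.007 at QWK 0.94, 0.011 at 0.90 and 0.015 at 0.86. A second simulation, with about 65% benign and QWK about 0.89, gave 0.0175. Clustering of slides within patients would raise these.

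Formula: expected optimism = SE × √(1 − ρ) × E[max of K standard normals].

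E[max] is 1.163 for K = 5, 1.867 for K = 20 and 2.249 for K = 50. √(1 − ρ) is 0.316 at ρ = 0.9 and 0.447 at ρ = 0.8.

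| K | ρ | Optimism in SE units | QWK at SE 0.010 | QWK at SE 0.020 |
|---|---|---|---|---|
| 5 | 0.9 | 1.163 × 0.316 = 0.37 | 0.004 | 0.007 |
| 5 | 0.8 | 1.163 × 0.447 = 0.52 | 0.005 | 0.010 |
| 20 | 0.9 | 1.867 × 0.316 = 0.59 | 0.006 | 0.012 |
| 20 | 0.8 | 1.867 × 0.447 = 0.83 | 0.008 | 0.017 |
| 50 | 0.9 | 2.249 × 0.316 = 0.71 | 0.007 | 0.014 |
| 50 | 0.8 | 2.249 × 0.447 = 1.01 | 0.010 | 0.020 |

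The range is about 0.004 to 0.02 QWK. A weaker correlation of 0.5 with K = 50 and SE 0.020 would give 2.249 × 0.707 × 0.020 = 0.032, but designs that differ by one modification at a time are likely to be more closely correlated than that.

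**Step 3: why this is upper-end.** The formula supposes that the best design was picked on KUH-1 alone. The protocol also uses cross-validation and two other tuning subsets, which dilutes the effect by an amount it does not allow one to compute.

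**The case against.** The strongest reply is that nothing is hidden and little hangs on it. The sentence that plans the comparison itself calls KUH-1 a tuning cohort, and the protocol says in advance that tuning sets serve comparison with existing models. No test, margin, ranking or superiority claim is attached. The Power section describes the aim as point estimates with intervals. The fairness wording introduces one measure, about image files, and need not be read as claiming equal tuning exposure. All of this stands, and it keeps the point modest. It does not remove the asymmetry, which Subgroup analysis F never mentions while placing the two comparisons side by side.

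A reader might also infer more than the documents support:

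- *That the whole comparison with the challenge algorithms is compromised.* The second comparison uses RUMC and STHLM3 validation data, which stay untouched until the freeze.
- *That KUH-1 alone determined the design or thresholds.* It is one of three tuning sources used beside cross-validation, and no text says that thresholds were set on KUH-1 specifically.
- *That there is training leakage.* Tuning cohorts are to be kept out of training and early stopping. The bias is one of selection.
- *That the plan breaks its own isolation rule.* That rule covers the validation cohorts, and tuning cohorts lie outside it.

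Finally, KUH-1 is the only set in Subgroup analysis F that is external to the development data in laboratory and scanner. That is a good reason to keep reporting it.

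**Conclusion.** The point holds in limited form. As written, the KUH-1 comparison favours the AI system through selection optimism, and neither identical image files nor bootstrap intervals over cases deal with it. The direction follows from the protocol's own account of the tuning set, together with the inference that a set labelled external validation was not used to tune the challenge algorithms. The size is unknown. The figure of 0.004 to 0.02 QWK depends on assumed values for everything except n = 330 and on selection from KUH-1 alone, so it should be read as an upper-end illustration, not an estimate.

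The importance is minor to moderate. It matters if a conclusion about the AI system against the state of the art is drawn from KUH-1. It does not touch the second comparison or the external validation cohorts on which the generalisation claim rests.

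**What to change.** In Subgroup analysis F:

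1. State that any comparative conclusion rests on the PANDA internal validation subset. Table 2 lists 333 RUMC and 212 STHLM3 slides for it, 545 together, against 330 in KUH-1.
2. Keep the KUH-1 comparison, but report it as descriptive and optimistic for the AI system because KUH-1 informed its design. Draw no superiority or ranking conclusion from it.
3. Confine the fairness wording to image format.

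Study status records the design lock on 16 August 2024, so the exposure cannot be undone and the remedy lies in reporting. It needs a few sentences and no new data or analysis. The real cost is that the conclusion would then rest on data from the same laboratories and scanners as the development set, where Study design itself expects optimistic estimates. That limitation should be stated alongside the result.

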### Sensitivity analyses

#### Sensitivity analysis A

We will evaluate the reproducibility of the AI system’s output in terms of the primary and secondary objectives on WSIs obtained from the same slides on multiple scanners. The analysis will be conducted on the STHLM3 tuning and internal validation cohorts and the MUL external validation cohort, which contain WSIs rescanned on different scanners (see table 1). In the STHLM3 cohort, a subset of slides (n=287) have been rescanned on five scanners: Aperio AT2 DX, Grundium Ocus40, Hamamatsu NanoZoomer 2.0-HT C9600-12, Hamamatsu NanoZoomer XR C12000-02 and Philips IntelliSite UFS. In the MUL cohort, a subset of slides (n=503) have been rescanned on two scanners: Grundium Ocus40 and Philips IntelliSite UFS. We will quantify the reproducibility of the AI predictions across scanners using QWK, and LWK and the percentage of slides with discordant predictions for each objective and each pair of scanners. We will additionally report confusion matrices.

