Subsets of the slides included in this study have been scanned multiple times. If the same slide had been rescanned multiple times on the same individual scanner (ie, the same physical device), we only kept the WSI with the latest scanning date, assuming the rescanning was due to, for example, initially poor focus or other scanning issues. Subsets of the STG, STHLM3 and MUL cohorts were rescanned with multiple different scanners (see table 1). To avoid biasing the evaluation towards these slides that appear in the dataset multiple times, we will only include one WSI per slide in the validation sets. For STHLM3, we will randomly select one WSI for each slide to be evaluated, and for MUL, we will use WSIs from the Grundium Ocus40 scanner, excluding those on the Philips UFS scanner. This ensures that the MUL cohort remains entirely external relative to the development data, considering that the STHLM3 cohort was partly digitised on the same Philips UFS instrument. The repeated scans will, however, be used during AI model development as an augmentation technique (except for the Grundium Ocus40 which is kept as an external scanner for validation), and for a separate cross-scanner reproducibility analysis (see section Statistical analyses).

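### Cross-scanner reproducibility of the cribriform and PNI outputs is tested partly on slides used to train those models, and two of its measures do not suit the millimetre cancer extent.

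*Protocol article*

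**What the plan says.** Sensitivity analysis A assesses reproducibility "in terms of the primary and secondary objectives on WSIs obtained from the same slides on multiple scanners". Its sample is fixed as follows: "The analysis will be conducted on the STHLM3 tuning and internal validation cohorts and the MUL external validation cohort". On numbers, "In the STHLM3 cohort, a subset of slides (n=287) have been rescanned on five scanners"; MUL contributes 503 slides on two scanners. Agreement is to be measured "using QWK, and LWK and the percentage of slides with discordant predictions for each objective and each pair of scanners", with confusion matrices in addition. The overview of statistical analyses lists the cross-scanner analysis under each of cancer extent, cribriform cancer and PNI.

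The section on cribriform cancer detection states: "The tuning set has an insufficient number of cribriform samples for evaluation and will be included in the training". The section on PNI detection says the same: "The tuning set has an insufficient number of PNI samples for evaluation and will be included in the training". Both limit their main evaluation to internal and external validation cohorts. The section on predefined data partitions confirms that STHLM3 contributes to the tuning set. It also says of slides scanned more than once: "The repeated scans will, however, be used during AI model development as an augmentation technique". It exempts only the Grundium Ocus40, which is held back as an external scanner.

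Cancer extent is an output in millimetres (System output). Its main analysis uses RMSE, with Pearson correlation and scatter plots.

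**The concern.** Two separate matters arise.

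**Training overlap.** A model trained on a slide tends to return the taught label for that slide, and more so if several scans of it were shown in training. Agreement between scanners on such slides says less about robustness on new slides. The cribriform and PNI sections respect this by dropping the tuning set from evaluation; Sensitivity analysis A brings it back without an exception. The protocol's own requirements for data partition ask that tuning cohorts stay independent of model training. Robustness across digitisation platforms is part of the study's stated objective, and the error would favour the AI.

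**Measures for extent.** Percent discordant and a confusion matrix presuppose categories. Sensitivity analysis A gives no bins, rounding or tolerance for millimetres, so what would be reported for extent is not determined by the text.

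**Working it through.** **1. Which slides and scanners are exposed.** For grading and extent, the article does not place the tuning set in training. For cribriform and PNI it does. Sensitivity analysis A has three parts:

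| Part | Training data for cribriform/PNI? |
|---|---|
| STHLM3 tuning | yes |
| STHLM3 internal validation | no |
| MUL | no |

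Five STHLM3 scanners give 5 × 4 / 2 = 10 pairs. Leaving out the Grundium Ocus40, four scanners remain that may have supplied augmentation scans, giving 4 × 3 / 2 = 6 pairs in which both scans could have been seen. In the other 4 pairs only one could. The article does not say how many tuning scans were used this way, but nothing excludes them.

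**2. Possible size (illustration; every input is an assumption).** Let s be the tuning share of the STHLM3 slides, d₀ the between-scanner discordance on held-out slides and d₁ that on training slides. The pooled discordance is d = s·d₁ + (1 − s)·d₀. With 20% positive calls on each scanner, chance agreement is 0.2² + 0.8² = 0.68, so kappa = (1 − d − 0.68)/0.32 = 1 − d/0.32.

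- d₀ = 10%, held-out only: 1 − 0.10/0.32 = 0.6875.
- s = 25%, d₁ = 5%: d = 0.0875, kappa 0.727.
- s = 25%, d₁ = 0: d = 0.075, kappa 0.766.
- d₀ = 5%, held-out only: 0.844. With s = 25%: 0.863 (d₁ = 2.5%) to 0.883 (d₁ = 0).
- Over s from 10% to 75%: 0.703 to 0.922 for d₀ = 10%, and 0.852 to 0.961 for d₀ = 5%.

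The width of these ranges shows that the result depends on figures the article does not give. It does not state s, nor whether the 287 slides are all within tuning and internal validation.

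**3. Binary outputs.** With two categories, linear and quadratic weights are both 0 or 1, so QWK, LWK and unweighted kappa coincide. A check on simulated binary calls gave 0.760 for all three.

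**4. Extent in millimetres.** Simulation of 2,000 slides, half with cancer, gamma-distributed extents (shape 1.5, scale 3 mm) and independent normal error per scanner, truncated at zero. All of these are assumptions. The discordance columns are among cancer slides; the others are over all slides without rounding.

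| Error SD (mm) | Discordant, no rounding | Rounded to 0.1 mm | Rounded to 1 mm | RMSE (mm) | QWK on mm | LWK on mm |
|---|---|---|---|---|---|---|
| 0.05 | 100.0% | 51.2% | 6.8% | 0.05 | 1.000 | 0.991 |
| 0.2 | 99.6% | 83.7% | 22.4% | 0.20 | 0.998 | 0.966 |
| 0.5 | 99.8% | 93.9% | 50.9% | 0.49 | 0.991 | 0.917 |
| 1.0 | 98.6% | 95.8% | 72.9% | 1.00 | 0.955 | 0.821 |

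Without rounding, percent discordant does not separate a 0.05 mm error from a 1 mm error. With rounding, the answer is driven largely by the unit chosen. RMSE follows the error directly.

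QWK on the millimetre values is 1 − mean(xᵢ − yᵢ)² / mean over all i, j of (xᵢ − yⱼ)². The denominator equals var(x) + var(y) + (x̄ − ȳ)², and the numerator is the same sum less 2·cov(x, y). QWK is therefore 2·cov(x, y) / [var(x) + var(y) + (x̄ − ȳ)²], which is Lin's concordance coefficient. The simulation agreed to three decimals.

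**The case against.** The strongest reply is that little is exposed. This is one sensitivity analysis. The main cribriform and PNI evaluations already leave out the tuning set, results are reported per scanner pair, and the 503 MUL slides give a clean Grundium–Philips comparison. Grundium scans were withheld from development, so 4 of the 10 STHLM3 pairs include a scanner the model was not trained on. The tuning set also holds few cribriform and PNI positives, so most positive calls may come from held-out slides, which could limit the effect on kappa. All of this stands, and it bounds the point. It does not remove it: a tuning slide in a Grundium pair may still have been seen on the other scanner, and the other 6 pairs lack even that protection.

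On extent, a rounding or tolerance rule could sit in a fuller analysis plan, and that is fair. But the article does fix a measure here by applying the same set to every objective. Elsewhere it matches measure to outcome: RMSE for extent, and in Sensitivity analysis B unweighted kappa for cribriform and PNI.

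A reader might infer that the secondary results as a whole are inflated, that the models have memorised the slides, or that weighted kappa is meaningless here. The documents support none of these. The overlap reaches only the tuning part of two outputs in one analysis; memorisation is not shown; QWK on millimetres is a recognised concordance measure, and LWK on millimetres can also be computed.

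**Conclusion.** The point holds in limited form. As written, the STHLM3 cross-scanner results for cribriform and PNI include training slides and may be optimistic. The direction favours the AI; the amount cannot be computed from the article, and the kappa figures above only illustrate it under assumed inputs. The main secondary analyses, the STHLM3 internal validation slides, MUL and grading are unaffected.

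For extent, percent discordant is uninformative and a confusion matrix undefined unless categories or a tolerance are set. This rests on reading the instruction to cover each objective literally, which the overview's listing of the analysis under cancer extent supports. Kappa on the binary outputs needs no change: the weighted forms are redundant there, not wrong.

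**What to change.** - **Cribriform and PNI:** in Sensitivity analysis A, restrict the sample to STHLM3 internal validation and MUL. Alternatively, report STHLM3 tuning slides separately, labelled as training data. State how many of the 287 slides fall in each part.
- **Cancer extent:** replace percent discordant and confusion matrices with between-scanner RMSE, matching the main extent analysis, or with mean difference and limits of agreement. Add a concordance coefficient.
- **Grading:** leave QWK, LWK, percent discordant and confusion matrices as they are.

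The cost is a few sentences, minor code and a smaller STHLM3 sample for two outputs. The model design is already locked, and neither change needs retraining or new data. Since the plan was published as prespecified, the change should be dated and recorded as an amendment.
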